##### Clinical Procedure After Treatment Initiation

After completion of baseline examinations, patients will receive flexible doses of the SSRI drug escitalopram, initially 5 mg for 3–5 days depending on side effects (e.g., nausea), followed by 10 mg daily until their first follow-up visit and further adjusted individually to a maximum dose of 20 mg. Escitalopram was chosen as it binds with high selectivity to the 5-HT transporter and has minimal affinity for other receptors (74). Patients are allowed short-time treatment with cyclopyrrolone (a nonbenzodiazepine hypnotic agent) or oxazepam (a benzodiazepine) to reduce anxiety and sleep disturbances which may be prominent in the initial treatment phase and have shown not to influence treatment continuation (75), but all are requested to avoid use 3 days prior to brain scans. Clinical follow-up sessions with a study physician or trained research assistant are scheduled in an out-patient clinical setting after 1, 2, 4, 8 and 12 weeks of treatment to evaluate treatment response and side effects. Visits can deviate a maximum of one week from the original time scheduled. No cognitive behavioral therapy or other psychotherapy program is provided during clinical visits. No treatment (pharmacological or psychotherapeutically) other than the medical monotherapy provided in this study is allowed elsewhere during the trial. At week 4, early non-responders (see definition below) or patients with unacceptable side effects are offered to switch to a standard second line antidepressant treatment; duloxetine (individually adjusted doses of 30–120 mg per day), which is a serotonin-norepinephrine reuptake inhibitor. Duloxetine was chosen according to clinical guidelines for second line antidepressant treatments. Cerebral 5-HT_4_R binding in humans is unaltered by injection of escitalopram (76). No prior *in vivo* studies have investigated the effect of duloxetine on 5-HT_4_R binding in the human brain, but *in vitro* work has shown that duloxetine has negligible affinity for the 5-HT_4_R (77). That is, none of the pharmacological compounds directly target 5-HT_4_R’s. The week 4 timepoint is in line with national guidelines in Denmark for switching to a second-line antidepressant treatment (4–6 weeks). Since our cohort receives frequent clinical follow-up sessions, patients can reach max dose of escitalopram (20 mg daily) already after 2 weeks. As such, switching after 4 weeks is considered appropriate for early non-responders in this trial set-up. All antidepressant medicine will be provided for free to improve compliance. Compliance will be assessed by serum escitalopram/duloxetine blood tests after eight weeks of treatment as well as tablet count at each follow-up. At each visit, depressive symptoms are rated using the HAMD_17_ and the HAMD_6_ subscale. HAMD_6_ captures core symptoms of depression more directly (and disregards sleeping quality), and has been found to be sensitive to antidepressant treatment response (69). Potential side effects due to intervention will be monitored at each visit using the “Udvalg for Kliniske Undersøgelser” scale (78). To ensure agreement and allow alignment of ratings, HAMD_17/_HAMD_6_ co-ratings between all the clinical investigators will be performed regularly during data collection. A maximum of 20% deviation from the “gold-standard” chief psychiatrist is allowed, or else a new satisfactory co-rating is needed before independent rating of study participants.

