Sexual dysfunction (e.g., low sexual desire, arousal difficulties, and anorgasmia) is a prominent feature of MDD, which often leads to a decline in quality of life (61, 62). Lack of interest to what is usually pleasurable, i.e., anhedonia, is a core symptom in MDD and may also be reflected in reduced sexual desire/interest. Sexual dysfunction, in particular anorgasmia and sexual arousal difficulties may further be linked to serotonergic dysfunctions (63) as seen in MDD. As a complicating factor, impaired sexual health related to MDD may worsen with antidepressant treatments targeting the 5-HT system. For example, in a group of 704 patients with MDD treated with an antidepressant drug (SSRI) or serotonin-norepinephrine reuptake inhibitor, about half of them developed or experienced worsening in their decreased sexual desire as a side-effect, which was also associated with reduced quality of life, lower self-esteem and adverse effects on mood and partner relations (62). We currently do not know which patient characteristics predict sexual dysfunction in response to SSRI treatment. However, differences in individual serotonergic brain architecture and/or serotonergic response to antidepressant treatment (e.g., SSRI) may play a role. In this study, we aim to map the frequency and predictors of SSRI induced sexual dysfunction and determine if serotonergic tonus (measured by 5-HT_4_R PET binding) pre-treatment, or changes in response to SRRI treatment, is associated with sexual desire and/or development of SSRI-induced sexual dysfunction in MDD.

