#### Psychometrics

Apart from clinical visits including HAMD_17/6_ ratings, patients will apply self-monitoring during the study period and fill out Danish versions of online questionnaires throughout the study. All questionnaires will be imported directly to an internal database through LimeSurvey, a free and open source software. Before EEG scans and cognitive testing, all participants will report their current mood state using an in-house Likert-scale. An adjusted Likert-scale will be filled out after each MR-scan. During visits at week 4, week 8, and week 12, patients are also asked to fill out a comprehensive set of self-rating state questionnaires (see **Table 1** for a full overview). Healthy controls will be asked to fill out selected state questionnaires as part of their baseline assessments.

**Table 1 T1:** Table over questionnaires obtained throughout the study.

Questionnaires	Time point					
	Baseline	Week1	Week 2	Week 4	Week 8	Week 12
**MINI**	X					
**HAMD-17/6**	X	X	X	X	X	X
**UKU**		X	X	X	X	X
**NEO-PIR**	X					
**CATS**	X					
**EHI**	X					
**OS-FHAM**	X					
**PBI-mother/father**	X					
**POMS***	X				X	X
**Likert-scale***	X				X	X
**BDI-II**	X			X	X	X
**MDI**	X			X	X	X
**PSS**	X			X	X	X
**SHAPS**	X			X	X	X
**RRS**	X			X	X	X
**CSFQ_F_C**	X			X	X	X
**SUSY item 32**	X			X	X	X
**Activity**	X			X	X	X
**GAD-10**	X			X	X	X

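### The UKU side-effect scale has no pre-treatment rating, so on that scale complaints present at entry cannot be separated from those that emerge on treatment

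*Protocol article*

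**What the plan says.** The section Clinical Procedure After Treatment Initiation names the UKU as the side-effect instrument: "Potential side effects due to intervention will be monitored at each visit using the" UKU scale. The follow-up sessions in that section are "scheduled in an out-patient clinical setting after 1, 2, 4, 8 and 12 weeks of treatment to evaluate treatment response and side effects".

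Table 1 in the Psychometrics section ("Table over questionnaires obtained throughout the study") gives the schedule. Its time points are "Baseline Week1 Week 2 Week 4 Week 8 Week 12". The HAMD row is filled throughout ("HAMD-17/6 X X X X X X"). The UKU row is blank under baseline and marked at the five later visits. The section on baseline assessments before treatment names no side-effect rating.

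Side effects also enter the trial's conduct: at week 4, besides early non-responders, "patients with unacceptable side effects are offered to switch to a standard second line antidepressant treatment". No UKU score or threshold is attached to that offer.

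The Introduction recognises that illness and drug complaints can overlap. It says that "Sexual dysfunction (e.g., low sexual desire, arousal difficulties, and anorgasmia) is a prominent feature of MDD", that antidepressants acting on serotonin may worsen it, and that cognitive disturbance is common in depression.

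**The concern.** A scale meant to pick up effects of the intervention needs a reference value from before the intervention. In a randomized trial a control arm could supply one. The Abstract describes a non-randomized open trial in which all patients are treated. The healthy controls are neither depressed nor followed on drug, so they cannot show what an untreated depressed patient would score. That leaves the patient's own pre-drug rating, and none is scheduled.

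This is more than a detail that an analysis plan might settle later. The article states the rating schedule, and no analysis can recover a baseline score that was never taken.

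Two things are at stake. The first is how UKU frequencies are read: a complaint rated at week 1 may be new, worse, unchanged or even improved since entry, and the score does not say which. The second is any comparison of UKU scores between response groups. Non-responders are defined by HAMD-6 scores that have not fallen enough. For UKU items that overlap with depressive symptoms, they could show more complaints than remitters even if the drug had caused none.

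**Working it through.** The plan gives no figure for this point, so the check consists of counting cells in Table 1, comparing passages, and asking what the data can identify.

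**1. Cell count in Table 1.** The table has 19 rows. Six instruments are given at baseline only (MINI, NEO-PIR, CATS, EHI, OS-FHAM, PBI). The other 19 − 6 = 13 are repeated:

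| Instrument | Baseline | On-treatment ratings |
|---|---|---|
| HAMD-17/6 | yes | 5 of 5 (weeks 1, 2, 4, 8, 12) |
| BDI-II, MDI, PSS, SHAPS, RRS, CSFQ, SUSY item 32, Activity, GAD-10 | yes | 3 of 5 (weeks 4, 8, 12) |
| POMS, Likert-scale | yes | 2 of 5 (weeks 8, 12) |
| UKU | **no** | 5 of 5 (weeks 1, 2, 4, 8, 12) |

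Thus 1 + 9 + 2 = 12 of the 13 repeated instruments have a baseline rating, and the UKU is the only one without. Its row fills the six columns with the first cell blank, so the gap does not look like a broken table.

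**2. Table against text.** The words on monitoring at every visit could, taken alone, include a baseline visit. But they stand under the procedure after treatment start, where the listed visits are weeks 1, 2, 4, 8 and 12. Those are exactly the five marked cells in the UKU row. Text and table agree that rating begins at week 1.

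**3. What the data can identify.** For one UKU item, let *p* be the proportion with the complaint at entry, *s* the proportion of those who still have it at a given visit, and *e* the proportion of the rest in whom it is new. The observed on-treatment frequency is

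f = p × s + (1 − p) × e.

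The planned ratings give only *f*. A frequency of new complaints needs *e*, and one equation does not determine three unknowns. With a baseline rating, each patient falls into a two-by-two table (before, after), and *p*, *s* and *e* can all be estimated. Worsening of a complaint already present can be seen only in that second case.

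**4. Comparison between response groups.** If *s* is higher in non-responders than in remitters, *f* differs between the groups even when *e* is zero in both. That is plausible for items overlapping with depression, since response is defined by the fall in depressive symptoms. The document gives no *p*, *s* or *e* for any item, so no size can be calculated.

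**5. Baseline information from other sources.** HAMD-17, BDI-II and GAD-10 cover mood, anxiety and related symptoms; CSFQ and SUSY item 32 cover sexual function; somatic and neurological status are examined before treatment; cognition is tested before treatment and at week 12. These show that a patient had a complaint in a given area at entry. They do not give a change score on the UKU.

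**6. Outcomes.** The primary outcome (remitter, intermediate responder, non-responder) and the secondary outcome (relative change) both use HAMD-6, which is rated at baseline. The Statistical Analyses section does not mention the UKU.

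**The case against.** The strongest reply is that the harm is not shown. The text speaks of potential side effects being monitored and gives no rule for counting or attributing UKU items. Such a rule may stand in the full protocol, which is not shown. A rater can also consult the other baseline scales and the somatic examination. The only research aim on side effects, sexual dysfunction under SSRI treatment, has CSFQ and SUSY item 32 at baseline and at weeks 4, 8 and 12. No UKU analysis is announced, and the Discussion says the trial is about biomarkers of response and not efficacy.

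Much of this stands, and it rules out several stronger readings:

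- A reader might infer that depressive symptoms will be counted as drug side effects. The document states no counting rule, so it supports only that they may be misattributed.
- A reader might infer that the week-4 switch offer is biased. It is not tied to a UKU score, and nothing says that clinicians disregard what they recorded at entry.
- A reader might infer that nothing seen on treatment can be separated from what was present at entry. That is too broad, given the other baseline measures; the limit applies to the UKU itself.
- A reader might take the passage allowing short-term medication "to reduce anxiety and sleep disturbances which may be prominent in the initial treatment phase" as evidence of complaints at entry. It describes the early treatment phase and does not establish their presence before it.
- A reader might want a percentage for the false attribution. Any such figure would rest wholly on assumed inputs.

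What the reply does not remove is the missing rating. A rule for attributing items, wherever it stands, would have to rely on recall, clinical judgement or other scales, because no earlier UKU score exists.

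**Conclusion.** The point holds in a limited form. On the schedule in Table 1, the UKU measures the prevalence of complaints during treatment. It cannot show which of them emerged or worsened on treatment, although the text presents it as a monitor of effects due to the intervention. Symptoms of depression present at entry may therefore be misattributed to the drug, and a UKU comparison of remitters with non-responders would be open to the same confusion.

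The weight is modest. The gap affects one instrument, which is neither the primary nor the secondary outcome, and other baseline measures cover part of it. The main predictor analyses are untouched. The size of any misattribution is unknown.

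The conclusion rests on two readings: that the blank baseline cell is the intended schedule, which the text supports, and that some UKU items overlap with symptoms of depression, which the article's own account of sexual and cognitive complaints makes likely.

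**What to change.** 1. For any patient not yet dosed, add a UKU rating at the existing pre-treatment visit and mark the baseline cell in Table 1. Report a side effect as an item that is new or has increased from baseline.
2. For patients without a baseline UKU, report frequencies as on-treatment symptom prevalence and not as drug-induced side effects.
3. In any UKU comparison between remitters and non-responders, state that persisting depressive symptoms can produce a difference without a drug effect.

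The first step costs one scale at a visit that already takes place, with a slightly longer baseline session. The other two cost a few sentences. They are probably the main route: the progress section says inclusion opened in August 2016, that collected material is being analysed, and that the data still to be collected concern healthy controls, so patient baseline visits appear to be largely past. Even with a baseline rating, the absence of an untreated patient arm means that the UKU would show change during treatment and not prove that the drug caused it; the report should say so.

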
##### Clinical Response Status

###### Primary Clinical Outcome Measure

The primary outcome measure is categorical and built to capture patients with an early as well as sustained, either excellent or poor response to treatment. Patients are classified as either “remitters”, “non-responders”, or “intermediate responders” after 8 weeks of treatment. These categories are based on percentage changes of depressive symptoms from baseline, as measured by HAMD_6_. Remitters must have ≥50% reduction in HAMD_6_ at 4 weeks (early responders) and a HAMD_6_ score <5 after 8 weeks of treatment. Non-responders have <25% reduction in HAMD_6_ after 4 weeks (early non-responder) and <50% reduction in HAMD_6_ after 8 weeks of treatment. Patients who do not meet the criteria above are defined as “intermediate responders” at week 8. The primary predictor analyses are directed to predict treatment response in a binary fashion (either remitter or non-responder (see **Figure 3**).

**Figure 3 f3:**
[figure not shown]
Response categorization for patients with MDD after 4 and 8 weeks of antidepressant treatment based on changes in HAMD_6_ score.

###### Secondary Clinical Outcome Measure

As a secondary outcome, we use a continuous response measure, i.e., HAMD_6_ changes from baseline at week 8 divided by HAMD_6_ at baseline, to allow analyses of the association between antidepressant treatment response and baseline characteristics or treatment-induced changes in the neurobiological modalities of interest.

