## Materials and Methods

**Figure 1** shows a flowchart of the scheduled data collection over the 12 weeks of pharmacological drug treatment of patients with MDD. Healthy controls (HC) will be recruited as specified below. Patients will be examined before (at baseline; week 0) and after 1, 2, 4, 8 and 12 weeks of SSRI treatment has been initiated. Depression-severity will be monitored by the Hamilton Depression Rating scale 17 items (HAMD_17_) and its subscale of 6 items (HAMD_6_) (69). A subset of patients will be offered re-examination with PET, fMRI, and EEG after 8 weeks of treatment, to assess changes from baseline and its association to treatment response. Patients from the whole spectrum of treatment responses (from poor to excellent) will be invited in a continuous fashion for this part of the study until allotted re-examinations are completed. All patients will also repeat cognitive testing at week 12. The power analysis in preparation of the study was primarily anchored to the PET modality. We estimated that we needed to include 100 patients to reach a statistical power of 80% to detect an association between treatment response (binary classification, i.e., remitters vs non-responders, see response-definition below) and baseline 5-HT_4_R non-displaceable binding potential (BP_ND_). These calculations were based on an expected 20% maximum drop-out, ~50% remission rate after 8 weeks of treatment (5, 6) and an expected difference of 8% in 5-HT_4_R binding between remitters and non-responders, corresponding to the previously found effect sizes on 5-HT_4_R change in BP_ND_ after fluoxetine treatment (18). Calculations were further based on an average BP_ND_ of 0.71 and a standard deviation of 0.073 (18, 70). With a rescan subgroup of approximately 40 patients, and a Gaussian distribution of change in BP_ND_ with an SD of 0.08 (log scale), we had an expected power of 80% to identify a significant association between longitudinal changes in BP_ND_ and changes in HAMD_6_ (i.e., secondary clinical outcome, continuous scale).

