### Statistical Analyses

#### Evaluating Associations Between Baseline Measures, Changes From Baseline Measures, and Clinical Outcomes

Baseline data from each modality of interest, i.e., PET, EEG, fMRI, MRI, cognitive measures, peripheral molecular markers, and clinical/demographic patient profiles, will be available for evaluating associations with the clinical outcomes for the entire group (n = 100 included). Changes from baseline data will be available for the subgroup (around n = 40 invited), who will be re-examined with brain scans and EEG for evaluating an association between changed measures and clinical outcomes. Similarly, cognitive follow-up data will be collected for all patients after 12 weeks of treatment. Primary analyses will test mean differences in baseline measures of the biomarkers from each modality between healthy controls and patients as well as response groups (remitter vs. non-responder at week 8, i.e., primary clinical outcome) using multiple linear regressions. This analysis focuses on the two extreme outcome groups. Secondary analyses will test the association between baseline measures of the biomarkers from each modality and antidepressant treatment response on a continuous scale, i.e., relative change in HAMD_6_, using linear multiple regression. This analysis incorporates the full spectrum of clinical outcomes. Similar analyses will be performed to study the association between the change from baseline measures of the biomarkers and the clinical outcomes. Regression models will be adjusted for age and sex, as well as modality-specific relevant covariates. For instance, 5-HTTLPR status is predictive of 5-HT_4_R binding (70) and will be adjusted for in the analyses concerning 5-HT_4_R. When relevant, interactions will be evaluated, e.g., we will test if the association between the clinical outcome and 5-HT_4_R is moderated by inflammatory status. Diagnostic regression tools will be used to assess model’s assumptions (e.g., linearity of the effects, normality assumption for residuals). When violated, corrective procedures will be used (e.g., splines and bootstrap resampling) (113). As appropriate, adjustments for multiple comparisons will be performed within each modality. In the analysis of the PET data, we will instead use a Latent Variable Model relating the 5-HT_4_R binding in several brain regions (neocortex, caudate nucleus, putamen and hippocampus) to treatment outcome *via* a latent variable (114). This allows us to assess the association between 5-HT_4_R binding and clinical outcome with a single test. Patients are considered with un-verified compliance if they have taken less than 2/3 of their antidepressant medicine, missed their week 8 visit, or have undetectable serum drug levels at week 8 (i.e., <10 nM for escitalopram and <15 nM for duloxetine). Patients with un-verified compliance will not be included in primary longitudinal analyses of treatment response. Missing data will therefore be handled using complete case analysis which in regression models is valid when the probability of dropping out of the study is, conditional on the covariates, independent of the outcome. If any participants were to be excluded during the study because of their clinical outcome, a sensitivity analysis will be performed.

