
#### Evaluation of the Predictive Value of the Biomarkers Within Modality

Logistic regression models for the primary clinical outcome will be used to obtain the probability of each patient to be a remitter (vs. a non-responder) based on its clinical data and the value of a modality-specific biomarker. Given a threshold (e.g., 0.5), patients with an estimated probability greater than the threshold will be predicted to be remitters, otherwise to be non-responders. The receiver operating characteristic (ROC) curve will be used to assess the compromise between sensitivity and specificity of this classification across thresholds. Since a 33% remission rate is expected in treatment regimen comparable to ours (5), we will focus on the ROC curve with high-specificity. The AUC (area under the curve) of the relevant part of the ROC curve will be reported as a summary of the predictive performance of each biomarker. The classification performance (accuracy, positive predictive value, negative predictive value) at the threshold optimizing the sum specificity and specificity will also be reported. To limit optimistic biases, these measures will be estimated using five-fold cross-validation (115). A permutation procedure will be used to obtain the null distribution of the predictive performance, against which the observed performance will be compared. Additional classification schemes may be considered (e.g., responder status as defined by ≥50% reduction in HAMD_6_ at week 8), with appropriate adjustment for inflated type-I error, to facilitate comparison of the current data with other relevant clinical trials. The predictor performance will be evaluated in a modality specific fashion and at a next stage, combined predictors will be evaluated.

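### The secondary models for relative HAMD_6 change do not name baseline HAMD_6 as a covariate, so a marker of baseline severity can appear to be associated with response, or a true association can be masked

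*Protocol article*

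**What the plan says.** Under Secondary Clinical Outcome Measure, the continuous outcome is "HAMD_6_ changes from baseline at week 8 divided by HAMD_6_ at baseline". Its stated purpose is to relate response to baseline characteristics and to treatment-induced changes in the neurobiological measures.

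Under Evaluating Associations Between Baseline Measures, Changes From Baseline Measures, and Clinical Outcomes, the secondary analyses relate each biomarker to "antidepressant treatment response on a continuous scale, i.e., relative change in HAMD_6_, using linear multiple regression". The covariate rule is "Regression models will be adjusted for age and sex, as well as modality-specific relevant covariates". The one example is for PET: "5-HTTLPR status is predictive of 5-HT_4_R binding (70) and will be adjusted for in the analyses concerning 5-HT_4_R". The PET data are analysed with a latent variable model over four regions instead of separate regressions. Similar analyses are planned for biomarker changes in the rescanned subgroup.

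The logistic prediction models in the next section do use each patient's clinical information ("based on its clinical data and the value of a modality-specific biomarker"), but they concern the binary primary outcome. Baseline HAMD_6 is not named as a covariate for the continuous outcome anywhere in the article.

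**The concern.** A ratio to baseline looks as if it has already dealt with baseline severity. It has done so only if, on average, the week-8 score is a fixed fraction of the baseline score. If not, relative change still rises or falls with baseline. Any biomarker related to baseline severity among patients then inherits a correlation with the outcome, even if it says nothing about response once severity is known. The same mechanism can cancel a real association when the two effects run in opposite directions.

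This outcome carries the analyses that use the full range of response, because the primary contrast compares only the two extreme groups. The rescan power is also stated for it. Baseline severity is common to every modality, so it does not naturally fall under modality-specific covariates.

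**Working it through.** **The plan's own figure.** Materials and Methods states 80% power for about 40 rescanned patients and the continuous outcome, but gives no slope or correlation, so it cannot be reproduced. With two-sided alpha 0.05 (assumed) and the Fisher z formula, r = tanh[(1.960 + 0.842)/√(n − 3)]. This gives |r| = tanh(2.802/√37) = 0.43 for n = 40, and 0.48 if 32 complete. Nothing here contradicts the 80%.

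**Inputs from the article.** There are 100 included patients ("will be available for evaluating associations with the clinical outcomes for the entire group (n = 100 included"). With the planning assumption of at most 20% drop-out ("These calculations were based on an expected 20% maximum drop-out, ~50% remission rate after 8 weeks of treatment"), 100 × 0.8 = 80 are evaluable. The rescan subgroup is about 40.

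**Assumed inputs (not in the documents).** Baseline HAMD_6 has mean 12 and SD 2. Week-8 HAMD_6 has mean 6 and SD 3.5. The baseline/week-8 correlation ρ runs from 0 to 0.6. The marker/baseline correlation m is 0, 0.3 or 0.5. Age and sex were not simulated.

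**Step 1: when the ratio is free of baseline.** If E[week 8 | baseline] = a + b × baseline, then E[relative change | baseline] = (b − 1) + a/baseline. This is constant only if a = 0. Here b = ρ × 3.5/2 and a = 6 − 12b.
- Proportionality (a = 0) needs b = 0.5, so ρ = 0.5 × 2/3.5 = 0.29.
- ρ = 0: b = 0, a = 6. Expected relative change is −0.40 at baseline 10 and −0.57 at baseline 14.
- ρ = 0.5: b = 0.875, a = −4.5. It is −0.575 at baseline 10 and −0.446 at baseline 14.

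The direction of the dependence therefore reverses on either side of ρ ≈ 0.29.

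**Step 2: rejection rate for a marker with no effect given baseline** (n = 80, 6,000 simulated trials per cell, scores rounded and kept within the scale):

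| ρ | correlation of relative change with baseline | unadjusted, m = 0.3 | unadjusted, m = 0.5 |
|---|---|---|---|
| 0 | −0.30 | 12.5% | 27% |
| 0.2 | −0.11 | 6.6% | 7.5% |
| 0.34 | +0.04 | 5.0% | 5.9% |
| 0.5 | +0.22 | 9.1% | 17% |
| 0.6 | +0.35 | 16% | 35% |

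With m = 0 the rate is about 5% throughout. With baseline HAMD_6 in the model it is 4.5–5.4% in every cell, whether the outcome is relative change or the week-8 score.

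**Step 3: hand check.** The induced marker/outcome correlation is about m times the second column. For ρ = 0 and m = 0.5 it is 0.5 × 0.30 = 0.15 in size. Then atanh(0.15) × √77 = 1.33, and the two-sided rejection probability is about 26%, against 27% simulated. For m = 0.3 the induced correlation is 0.09, giving about 12%, against 12.5%.

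**Step 4: sensitivity.** With week-8 mean 5.5 in place of 6, the rates for m = 0.3 and 0.5 are 10% and 24% at ρ = 0, about 5–6% at ρ = 0.3, and 12% and 19% at ρ = 0.5. With weaker links to severity over ρ = 0 to 0.5 they are 5–6% (m = 0.1) and 5–7.5% (m = 0.2).

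**Step 5: n = 40.** For m = 0.3 and 0.5 the rates are 7.8% and 16% at ρ = 0, and 7.2% and 11% at ρ = 0.5. The highest in the grid is 20% (ρ = 0.6, m = 0.5).

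**Step 6: power for a true effect** (partial correlation 0.3, n = 80). If the marker is unrelated to baseline, unadjusted power is 70–76%, against 76–77% for the week-8 score adjusted for baseline: a gain of about 1 to 6 points. If the marker/baseline correlation is ±0.3, unadjusted power ranges from 27% to 92%, against 74–78% adjusted.

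**The case against.** The strongest reply is that the covariate list is open: it speaks of relevant covariates and offers 5-HTTLPR as an example. This is a condensed article, and a statistical analysis plan or the appendix could add baseline HAMD_6. That is possible. But the article does fix an outcome and a covariate rule for it, and baseline severity is not a modality-specific term. Naming it is a concrete improvement to what is stated, not a complaint about missing detail.

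Second, for the marginal question of whether a marker is associated with relative change, the induced correlation is real, so rejecting zero is not an error. This stands. The excess rejections are false only for the question of whether a marker carries information beyond baseline severity. That is the more useful question for a predictor, since severity is already known.

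Third, the size depends on inputs that the article does not give. This also stands. A reader might infer that the article itself expects within-patient correlations of 0.3–0.5 with severity. It does not. The introduction's amygdala and inflammation material largely concerns patients versus controls, and for cognition it describes a dissociation from mood symptoms. The entry threshold on HAMD_17 also truncates low severity.

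Fourth, relative change fits the percentage-based response categories, so discarding it would break that link. This is accepted. Making the week-8 score the outcome in the PET latent variable model, where binding appears to be the modelled response, would restructure that model without need.

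**Conclusion.** The point holds as a conditional weakness of the secondary continuous analyses. For a marker with no effect given baseline, and with 80 patients, the rejection rate is about 5% when the week-8 score is close to proportional to baseline or the marker is unrelated to severity. It is roughly 10–25% when the marker correlates 0.3–0.5 with severity and the baseline/week-8 correlation is 0 or 0.5. The inflation is smaller at 40 patients. All of this rests on assumed HAMD_6 means, standard deviations and correlations. With baseline in the model the rate is about 5% whichever values are true.

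Three stronger readings are not supported. One is that the plan will generally produce false positives: near proportionality it would not. Another is that substantial precision is lost: the gain for a marker unrelated to severity is at most about 6 power points. The third is that the primary result is compromised: the remitter versus non-responder contrast uses a different outcome, and this finding does not touch it.

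**What to change.** In the statistical section, name baseline HAMD_6 alongside age and sex as a covariate in all models for the continuous outcome. This covers the regressions on baseline biomarkers, the analyses of biomarker change in the rescan subgroup, and the PET latent variable model. Keep relative change as the defined outcome.

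In the ordinary regressions, the week-8 HAMD_6 score adjusted for baseline is a near-equivalent alternative. The article does not say whether the biomarker or the response is the dependent variable. With the same covariates in a linear model, the test of their partial association is the same either way, so adding the covariate works in both cases.

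The cost is one degree of freedom and one sentence. Baseline HAMD_6 is already collected for every patient.
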